**Figure 1 figure1:**
[figure not shown]
Overview of the participant flow for the randomized controlled trial.

### Sample Size

Previous meta-analyses assessing drinking reduction in young adults compared to assessment only, attention-matched, or active controls [17,18] found small effect sizes of about g=0.25. Although we expect the Boozebuster intervention to outperform previous interventions in reducing the quantity and frequency of alcohol consumption in comparison to the control condition at the posttest assessments, we decided to base our sample size calculation on this conservative effect estimate. These estimations would result with α=.05 and 1–β=.80 in a sample size of 253 per study arm (ie, N=506).

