The majority of the above-described digital interventions are delivered via a computer or web browser. However, it has been claimed that mobile apps are more suitable for young adults given the flexibility, interactivity, and their spontaneous nature [12]. However, a recent review assessed mobile apps developed with the purpose of managing alcohol consumption found that the evidence is promising but still inconclusive given the mixed results [13].

Although single-session interventions can reach a high number of individuals due to their appealing, limited time requirement, they are associated with a few important disadvantages such as the relatively small effect sizes produced and the limited longevity of those effects. For example, meta-analyses assessing single-session interventions show small effect sizes when compared to assessment only, attention-matched, or active controls ranging from g=0.18 to g=0.29 [5,14-18]. In addition, studies that assess long-term outcomes often show that those effects cease to exist in follow-up periods [19]. Lifestyle medicine is a relatively new approach for the potential prevention, promotion, and management of mental health conditions. It involves the use of environmental, behavioral, and psychological principles to improve physical and mental well-being by modifying lifestyle factors such as diet, physical activity, relaxation, sleep, and stress [20]. Although lifestyle modification has been extensively studied in particular regarding the prevention of chronic diseases [21], research about its value in curbing drinking among young adults is very limited. However, studies have shown that digital lifestyle interventions that target multiple behaviors may increase and prolong the effectiveness of behavioral change interventions targeting young adults [22-24].

Therefore, in our intervention, we decided to incorporate relevant lifestyle components that have been shown to be perceived as relevant and important for our target group’s general well-being [25-27]. Such lifestyle-related topics include sleeping habits, mood, and perceived stress. We expect that by providing young adults with relevant lifestyle components in addition to the alcohol-related intervention content, we have a potential to increase and prolong effect sizes regarding drinking outcomes, while retaining the acceptability and reach of single-session interventions.

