### Statistical Analyses

After the data collection period, we will clean our data and assess it for accuracy and completeness. Missing data will be handled using either multiple regression imputation techniques or full information maximum likelihood estimation, depending on the amount of missing data and whether it is missing at random or not. All analyses for the primary and secondary outcomes will use linear mixed modeling regression analyses with the three time points nested within participants. For continuous outcomes, linear models will be used for normally distributed data and negative binomial models, for left-skewed data. For dichotomous outcomes, such as whether or not participants had a binge-drinking episode in the past 30 days, binary logistic regression will be used. All primary analyses will be conducted in line with the intention-to-treat (ITT) principle (ie, including all participants that are randomized). Sensitivity analyses will be conducted in line with the per-protocol principle (ie, intervention completers) and with study completers only. All statistical tests use a significance level α=.05. Time will be used as predictor and baseline measures will be included as covariates if appropriate. All analyses will be conducted using the R Statistical Package. Cohen *d* values will be used as the measure of effect size. Effect sizes of 0.8 are assumed to be large, effect sizes of 0.5 are assumed to be moderate, and effect sizes of 0.2 are assumed to be small [69]. In addition, several intervention effect moderators that might moderate drinking levels based on findings of previous studies will be investigated. In addition, potential moderators such as gender [70], readiness to change [71], engagement [72], and impulsivity [73] will be explored.

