## Results

Our study began recruitment in September 2020. We received 933 registrations on our study information website. Of these registrations, 506 participants have completed the baseline assessment, 336 participants have completed the 6-week postbaseline assessment (T1), and 308 participants have completed the 3-month postbaseline assessment (T2) as of May 2021. The study is still in progress. Results will be reported in 2021 and 2022.

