### Potential Strengths and Limitations

Our study has a number of strengths such as the delivery of our intervention via the use of a mobile app, which seems to be a feasible and desirable delivery method for our target group [74,75]. Second, this study used an open recruitment strategy, which will enhance the generalizability of our results compared to studies that recruit only in university settings. Given the large sample size we aim to recruit, our study will provide a reliable estimate regarding the effectiveness of our mobile intervention.

Nevertheless, there are some limitations that are worthwhile mentioning. We are measuring all outcomes via self-report measures, and we have decided against using lengthy and costly diagnostic interviews in order to reach out to a large sample group and due to the preventive nature of our intervention. However, based on the literature, we know that self-report measures are reliable for actual drinking levels in our target population [76]; furthermore, we expect that the EMA function that we included for self-monitoring purposes will augment and improve our assessments by adding a dynamic dimension to it [41]. We expect a potential large dropout rate at posttest and 3-month follow-up assessments as commonly observed in web-based interventions with an open recruitment strategy [77]. To minimize drop-out, automated reminders for completing questionnaires will be sent via email to our participants and participants will be offered financial incentives for completing the follow-up assessments.

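### The sample size of 253 per arm makes no allowance for dropout that the protocol itself expects to be large, so the stated 80% power is unsupported as written

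*Protocol article*

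**What the plan says.** The Sample Size section takes its effect from earlier meta-analyses, which "found small effect sizes of about g=0.25", and concludes that, with α of .05 and power of .80, this would result "in a sample size of 253 per study arm (ie, N=506"). It refers the comparison to the posttest assessments. It mentions no dropout rate, no correlation between repeated measurements and no baseline adjustment. The Abstract gives 506 as the number to be recruited, and the Results give 506 as the number who completed baseline.

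Under Potential Strengths and Limitations the protocol says: "We expect a potential large dropout rate at posttest and 3-month follow-up assessments". Its response is reminders and financial incentives, not a larger sample. The Results then report that "336 participants have completed the 6-week postbaseline assessment (T1), and 308 participants have completed the 3-month postbaseline assessment (T2") as of May 2021, with the study still in progress.

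The Statistical Analyses section plans mixed models with the three time points nested within participants, and multiple imputation or full information maximum likelihood for missing data. Baseline measures enter as covariates only where judged appropriate. On the test level it says: "All statistical tests use a significance level α=.05".

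**The concern.** A sample-size calculation gives the number of participants who must contribute outcome data. If that number is also the number recruited, the stated power holds only when nobody is lost. Here the same article expects substantial loss and already reports it. The sample-size statement and the dropout statement therefore do not fit together.

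What is at stake is how the result is read. If the trial finds no difference, a reader who takes the stated power at face value would put the chance of missing an effect of 0.25 at 20%. On the unadjusted calculation with the reported completers, that chance is about 37% at T1 (100 − 63) and 41% at T2 (100 − 59). The limitations section also relies on the sample size when it says that the trial will give a reliable estimate of effectiveness.

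**Working it through.** **Inputs from the protocol.** Standardised difference d = 0.25, α = .05, power .80 (Sample Size); 1:1 allocation (Randomization); 506 with baseline, 336 with T1 and 308 with T2 data (Results).

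**Assumptions.** The test is two-sided, which the protocol does not state; a one-sided test would need 198 per arm, so only the two-sided reading gives 253. Completers are split equally between arms: 336/2 = 168 at T1 and 308/2 = 154 at T2.

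**Step 1: reproduce the stated figure.** The exact two-sided two-sample t test needs 252.13 per arm, rounded up to 253, with power 80.1%. The normal approximation gives 252. The match is exact with no dropout term and no baseline-correlation term.

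**Step 2: loss to date.** 1 − 336/506 = 33.6% at T1; 1 − 308/506 = 39.1% at T2.

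**Step 3: the same calculation with the reported completers.** Power ≈ Φ(d·√(n/2) − 1.960), with n per arm.
- Full data: 0.25 × √(253/2) = 2.812; Φ(0.852) = 80.3%.
- T1: 0.25 × √(168/2) = 2.291; Φ(0.331) = 63.0% (t test 62.7%).
- T2: 0.25 × √(154/2) = 2.194; Φ(0.234) = 59.2% (t test 59.0%).

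**Step 4: effect detectable with 80% power.** (1.960 + 0.842) × √(2/n) gives 0.306 for n = 168 and 0.319 for n = 154, against the planned 0.25.

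**Step 5: smaller losses.** Because the counts are interim, the same formula for losses of 10%, 20% and 30% gives 76%, 71% and 65%.

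**Step 6: what baseline adjustment could recover at one visit.** Adjusting for a baseline value with correlation r to the outcome multiplies the residual SD by √(1 − r²). The protocol gives no r, so a range is assumed:

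| r | T1 (168 per arm) | T2 (154 per arm) |
|---|---|---|
| 0 | 63% | 59% |
| 0.3 | 67% | 63% |
| 0.5 | 75% | 72% |
| 0.7 | 89% | 87% |

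Setting power to 80% and solving, r = √(1 − (n/2)(0.25/2.802)²), which is 0.58 at T1 and 0.62 at T2.

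**Step 7: what joint use of both visits could recover.** Take as contrast the average group difference over T1 and T2, adjusted for baseline. Assume an effect of 0.25 at both visits and one common correlation r among the three measurements. The variance factor is (1 + r)/2 − r², that is 0.56, 0.50 and 0.36 for r = 0.3, 0.5 and 0.7. With 154 per arm, power is 83%, 87% and 96%; with 168 per arm it is 86%, 90% and 97%. If everyone with T2 data also has T1 data, the true figure lies between the two.

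**The case against.** The strongest reply is that the unadjusted single-visit test is not the planned analysis. The plan is a mixed model over T0, T1 and T2, and Step 7 shows that a baseline-adjusted average of the two follow-up visits could exceed 80% at the reported retention. That stands. A reader might infer from the completer counts that the trial has failed to deliver its 80% power, and the documents do not support that. They name neither the contrast nor a correlation. For T2 alone with baseline adjustment, power runs from 63% to 87% over r = 0.3 to 0.7. The protocol's power statement draws on none of this, so the model does not rescue the figure as stated either.

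Second, the counts are a snapshot, and the article does not say how many assessments were still due. This also stands: 34% and 39% are upper bounds on the final loss. The missing allowance does not depend on them, since Step 5 shows a shortfall even at 10% loss.

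Third, intention-to-treat analysis with imputation or full information maximum likelihood keeps all 506 in the model. Under missing at random this addresses bias. It does not by itself replace follow-up information that was never observed.

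A further tempting criticism concerns the choice of 0.25, since the authors write "we decided to base our sample size calculation on this conservative effect estimate" while the Introduction cites effects "ranging from g=0.18 to g=0.29". A reader might infer that the estimate is optimistic because it lies above the middle of that range. This does not hold. In context the word is relative to the authors' expectation that their app will do better than earlier interventions, and the midpoint of a range across several meta-analyses is not an estimate of anything.

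**Conclusion.** The arithmetic behind 253 per arm is correct; the use made of it is not. It is a requirement for complete data, applied as a recruitment target in a trial that expects large dropout. The stated 80% is therefore unsupported as written. With an equal split and the May 2021 counts, the protocol's own form of calculation gives about 63% power at T1 and 59% at T2, with detectable effects of about 0.31 and 0.32. These figures are the low end if further assessments come in. Whether the planned model reaches 80% cannot be settled from the protocol: it depends on the contrast, the correlations and the use of baseline, the first two of which are not stated and the third of which is left conditional.

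**What to change.** No further enrolment is needed.

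1. In the Sample Size section, describe 253 per arm as the number with outcome data that an unadjusted two-sided comparison at one visit requires, and say that no dropout allowance was made.
2. Once follow-up closes, report power for 0.25 and the effect detectable with 80% power at the retention reached.
3. Name the primary contrast (T1, T2 or their average) and give the corresponding power for the planned model over a stated range of assumed correlations, in the manner of Steps 6 and 7.
4. Replace the conditional wording on baseline with one fixed choice for the primary model: either T0 as a covariate with T1 and T2 as outcomes, or T0 as an outcome with the baseline means of the two arms constrained to be equal. Not both, since that would use the same measurement twice.

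The cost is a less favourable power statement and a firm commitment on the primary analysis.

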### Intervention

Boozebuster is a mobile app aimed at developing low-risk drinking habits in young adults according to the Dutch drinking guidelines. It has been developed by Vrije Universiteit Amsterdam in collaboration with the Institute for Systems and Computer Engineering, Technology and Science [30]. Boozebuster is based on the Moodbuster platform, which is being used for a variety of research projects funded by the European Union [31,32].

Boozebuster focuses on the importance of the individuals’ motivation, self-efficacy, and environmental constraints with regard to drinking. The behavioral change techniques used include PNF [18], motivational interviewing [33], cognitive behavioral therapy [34], goal setting [35], self-monitoring [36], protective behavioral strategies [37], and mindfulness [38].

Boozebuster contains a total of seven modules and was developed with the following rationale in mind: the PNF module serves as the first assessment of young adults’ drinking patterns and compares it with peer norms and the official Dutch drinking guidelines [39]. This procedure creates awareness among the individuals about their alcohol consumption in relation to their peers and has shown to be an effective approach in initiating drinking-related changes [40]. The incorporated motivational interviewing module motivates the individuals to change their alcohol-related behaviors by assisting them in building confidence in their abilities for achieving their goals. In addition, Boozebuster includes a variety of lifestyle support modules, such as relaxation, improving sleep, drinking diary, gratitude diary, and an emergency button specifically designed to provide recommendations for acute cravings. These modules provide individuals with tools to deal with cravings, peer pressure, and stress that might otherwise interfere with their drinking-related goals.

Participants in the Boozebuster group will be able to monitor their daily alcohol consumption via ecological momentary assessments (EMA) [41] in terms of the amount of standard drinks consumed, their mood via daily mood ratings on a scale of 1 (low) to 10 (high), and their sleep quality via daily sleep quality ratings on a scale of 1 (low) to 10 (high). Participants will also be able to monitor their progress on the three abovementioned key behaviors (ie, drinking, mood, and sleep) via visual feedback (ie, visualization of their scores) through the mobile app.

Participants are free to use Boozebuster during the 6-week study duration as frequently as desired. The reason we opted for a 6-week period is because it is the recommended timeframe in which alcohol-related changes can occur and be measured [42]. Hence, participants will be stimulated and motivated to engage with our intervention via the daily reminders of the EMA function during the 6 weeks of study participation. Figure 2 provides an overview of the Boozebuster mobile app and its modules.

**Figure 2 figure2:**
[figure not shown]
Screenshot of the Boozebuster mobile app (home screen).

### Educational Website Condition

Participants in the control condition will receive access to an educational website containing information on the effects and consequences of alcohol use on health. Only participants allocated to the control condition will have access to this website.

### Outcome Measures

Given that applied outcome measures in the alcohol intervention literature vary considerably we decided to follow the advice and included key outcomes based on the recommendation of the Outcome Reporting in Brief Intervention Trials on Alcohol (ORBITAL) framework [43].

#### Primary Outcomes

##### Alcohol Consumption, Frequency, and Quantity

The primary outcome is the quantity and frequency of alcohol consumption in terms of standard drinks (10 g ethanol per standard drink) per month; this will be assessed through the timeline follow-back (TLFB) method [44], which measures alcohol consumption during the prior 30 days in terms of number of standard drinks. The TLFB is widely used in obtaining data on the frequency of occurrence of drinking behavior, has been evaluated in various clinical and nonclinical populations, and has been shown to have good psychometric characteristics [45,46].

#### Secondary Outcomes

##### Intervention Adherence

Intervention adherence will be calculated descriptively based on the percentage of participants who completed the main PNF and motivational interviewing module.

##### Readiness to Change

The Readiness to Change Questionnaire (RCQ) [47] is a 12-item self-report questionnaire assessing participants’ readiness to change according to the three stages of change: precontemplation, contemplation, and action. The items are rated on a 5-point scale from –2 (totally disagree) to 2 (totally agree). The scores of each stage of change are calculated by adding the individual item scores of the relevant scale. The range of each scale is –8 through 0 to +8. A negative score indicates an overall disagreement with the items measuring the particular stage of change, whereas a positive score represents overall agreement. The RCQ has previously been applied in Dutch clinical settings and has proven to be a reliable and valid tool to measure an individual’s readiness to change [48,49].

##### Binge Drinking

Participants will be asked to indicate the number of binge-drinking days defined as 4 (for females) or 5 (for males) standard drinks on one drinking occasion over the past 30 days.

##### Alcohol-Related Problem Severity

Alcohol-related problem severity will be assessed via the Rutgers Alcohol Problem Index (RAPI) [50]. The RAPI is an 18-item self-reporting scale that measures alcohol-related problems. The questions are answered on a 4-level scoring system, with higher scores indicating higher levels of alcohol-related problems. The total score is derived by summing the individual scores for each of the 18 items on a scale of 0 to 3; consequently, total scores range from 0 to 54. The RAPI is widely used to assess alcohol-related problems in adolescents and university students and is considered reliable and valid [50].

##### Cannabis Use Frequency and Quantity

Cannabis use frequency was assessed using the TLFB method [51]. Furthermore, we asked participants to estimate the quantity of cannabis consumed (in grams) during the previous 30 days. The TLFB method has shown to collect reliable and psychometrically sound information about individuals’ daily cannabis use [52].

##### Depressive Symptoms

Depressive symptoms will be assessed via the Center for Epidemiological Studies Depression (CES-D) scale [53], a 20-item self-report scale designed to measure depressive symptoms. The CES-D has been tested in various settings and is considered a reliable and valid tool to measure depressive symptoms in a variety of populations also including young adults [54]. Responses are based on the frequency of occurrence of depressive symptoms. The questionnaire uses a 4-point ordinal scale: 0 (not at all), 1 (several days), 2 (more than half the days), and 3 (nearly every day). The scores of the CES-D scale range between 0 and 60, with cut-off scores of 16 and 20 indicative of mild depressive symptoms, scores between 21 and 25 are indicative of moderate depressive symptoms, and scores between 26 and 60 suggest severe depressive symptoms [55].

##### Mental Well-being

The Warwick-Edinburgh Mental Wellbeing Scale (WEMWBS) [56] is a 14-item self-report scale that measures positive mental well-being. The items are rated on a scale of 1 (none of the time) to 5 (all of the time). Higher scores indicate higher levels of positive mental well-being among respondents. The WEMWBS has been previously validated in a Dutch setting and has proven to be a reliable and valid tool to measure individuals’ mental well-being [57].

##### Perceived Stress

The Perceived Stress Scale (PSS) [58] is a 10-item self-report scale that measures perceived stress. The questions are answered on a 5-level scoring system in which higher scores indicate higher levels of perceived stress. The total score is derived by summing the individual scores for each of the 10 items on a scale of 0 to 4; consequently, total scores range from 0 to 40. The PSS is considered a reliable and valid screening tool for perceived stress [59].

##### Study or Work Performance

The task performance scale is a 5-item self-report scale that measures study or work performance and is part of the Individual Work Performance Questionnaire [60]. The total score is derived by summing the individual scores for each of the 5 items on a scale of 0 to 4; consequently, total scores range from 0 to 20. The task performance scale is considered a reliable and valid screening tool for measuring study or work performance among adults [61].

